### Sample Size

At least 42 patients with breast cancer will be recruited for the study. The patients will be divided into 3 experimental groups, each consisting of 14 patients, based on the type of treatment performed (tDCS only, exercise therapy only, or combined treatment). In case of dropouts, the recruitment of patients will continue until 42 participants complete the treatment.

Since the present study is the first to evaluate the effects of tDCS in patients with different types of chronic pain over a 3-week period, to estimate the expected difference between the effect of tDCS and combined therapy (tDCS and exercise therapy), for the calculation of the sample size we relied on a recently published study [54] of 45 patients with fibromyalgia to calculate the sample size. The published study compared the effects of tDCS and exercise therapy if carried out individually or in combination for 1 week. The improvements observed in the 3 treatment groups are shown in the Table 4.

**Table 4 table4:** Mean visual analogue scale (VAS) scores of the different treatment groups.

Treatment group	Baseline VAS	Improvement (%)	VAS at 1 week after treatment	ΔVAS (beginning of treatment vs 1 week after treatment)
tDCS^a^	7.2	18	5.904	1.296
Combined therapy	7.3	40	4.4019	2.8981
Exercise therapy	6.8	24	5.202	1.598

^a^tDCS: transcranial direct current stimulation.

The sample number for each individual clinical center was calculated to demonstrate the difference between the change in the visual analogue scale (VAS) value at the beginning of treatment and after 1 week of treatment between the group of patients receiving tDCS and that receiving combined therapy. A Wilcoxon-Mann-Whitney test was performed using G*Power V3 software [57] with an effect size of 1 and assuming the following parameters: a VAS change of 1.3 in the tDCS treatment group and 2.9 in the combined therapy group, as reported by Mendonca et al [54] in the evaluation after 1 week of treatment; an SD of 1.27 in both groups; a type 1 error of 0.05; and a power of 80%. A sample of the same size is adequate to demonstrate the difference in VAS between the exercise therapy group and the combined therapy group (based on data from Mendonca et al [54]).

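### The stated effect size of 1 disagrees with the printed means and SD (d = 1.26), and at alpha 0.05 the 14 per group follows only from d = 1 with an undeclared one-sided test

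*Protocol article*

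**What the plan says.** The Sample Size section of the protocol article plans three arms of equal size: "The patients will be divided into 3 experimental groups, each consisting of 14 patients". The calculation targets the difference between tDCS alone and combined therapy in VAS change from the start of treatment to 1 week. The test and program are given: "A Wilcoxon-Mann-Whitney test was performed using G*Power V3 software". The inputs follow in the same sentence: "with an effect size of 1 and assuming the following parameters: a VAS change of 1.3 in the tDCS treatment group and 2.9 in" (the second change being that of combined therapy). The sentence ends with the remaining inputs: "an SD of 1.27 in both groups; a type 1 error of 0.05; and a power of 80" percent.

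The section adds that this size is also sufficient for exercise therapy versus combined therapy. For that pair, Table 4 shows VAS changes of 1.598 and 2.8981. No separate SD or effect size is given.

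Neither this section nor Statistical Analysis says whether tests are one- or two-sided. Statistical Analysis mentions type 1 error correction for the group comparisons, without saying how it is done or whether it entered the sample size.

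**The concern.** For two groups with a common SD, the effect size is the difference in means divided by that SD. All three quantities are printed and they do not fit together. Rounding does not explain it, since 1.26 rounds to 1.3. Nor is this a detail that an article leaves to a fuller document, because the conflict lies between figures that are all on the page.

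This paragraph is the only justification given for 42 patients. As it stands, a reader cannot tell which effect size, test direction or alpha per comparison the trial was planned on. Depending on the answer, power at 14 per group lies on either side of the stated 80%.

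**Working it through.** **Inputs** (Sample Size section and Table 4): changes of 1.3 (tDCS) and 2.9 (combined); SD 1.27; stated effect size 1; alpha 0.05; power 80%; n = 14 per group; Wilcoxon-Mann-Whitney test. Exercise therapy: change of 1.598 against 2.8981 for combined.

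**Assumption:** a normal parent distribution, because the article does not give the G*Power setting. The asymptotic relative efficiency (ARE) is then 3/π = 0.955.

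**Step 1, effect sizes.**
- tDCS versus combined: (2.9 − 1.3)/1.27 = 1.6/1.27 = 1.26. For d = 1 with this difference, the SD would have to be 1.6.
- Exercise versus combined: (2.8981 − 1.598)/1.27 = 1.30/1.27 = 1.02, if SD 1.27 also applies here.

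**Step 2, formula.** With n per group, power comes from a noncentral t distribution with df = 2n·ARE − 2 and noncentrality d·√(n·ARE/2). At n = 14, df = 2 × 14 × 0.955 − 2 = 24.7 and √(14 × 0.955/2) = 2.585. The noncentrality is therefore 2.59 for d = 1, 3.26 for d = 1.26 and 2.65 for d = 1.02. The critical value at alpha 0.05 is 1.709 one-sided and 2.061 two-sided.

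**Step 3, reproducing the plan's figure.** With d = 1 and one-sided 0.05, n = 14 gives 80.8% and n = 13 gives 78.0%. So 14 is reproduced exactly under that pairing.

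**Step 4, the alternatives at alpha 0.05.**

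| Comparison and d | Sides | n per group for 80% | Power at 14 |
|---|---|---|---|
| tDCS vs combined, d = 1 (stated) | one | 14 | 81% |
| tDCS vs combined, d = 1 (stated) | two | 18 | 70% |
| tDCS vs combined, d = 1.26 (means and SD) | one | 9 | 94% |
| tDCS vs combined, d = 1.26 (means and SD) | two | 12 | 88% |
| Exercise vs combined, d = 1.02 | one | 14 | 82% |
| Exercise vs combined, d = 1.02 | two | 17 | 72% |

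Simulation of the exact test at 14 per group (20,000 runs) agrees. For d = 1, 1.26 and 1.02 it gives 70%, 88% and 73% two-sided, and 80%, 93% and 82% one-sided.

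**Step 5, sensitivity to the parent distribution.** With G*Power's minimum-ARE option (0.864), two-sided power at 14 is 65% for d = 1, 84% for d = 1.26 and 67% for d = 1.02. With a logistic parent it is 76%, 92% and 78%. A Laplace parent would lift all three above 80% (89%, 98% and 90%), but nothing in the article points to that choice. At alpha 0.05, none of these options makes 14 the required n, with either effect size and either sidedness.

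**Step 6, a split alpha.** With d = 1.26 and two-sided 0.025 (0.05 divided over two comparisons), n = 14 gives 80.2% and n = 13 gives 76.5%. This also returns 14, but the stated type 1 error is 0.05. On the same basis, exercise versus combined (d = 1.02) has 61% power.

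**The case against.** The tempting stronger reading is that the 80% power statement is simply wrong. The documents do not support that. The article never says that the test is two-sided, and d = 1 with one-sided 0.05 gives 14 exactly. The printed means and SD need only 12 per group at two-sided 0.05, so for the comparison that the calculation names, 14 exceeds 80%. The fall to 70% needs d = 1 paired with a two-sided test, and the article does not state that pairing.

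A reader might also infer that the trial will be tested one-sided, with a doubled error rate in favour of the combination. That does not follow either. Statistical Analysis specifies no one-sided test, and a split alpha with d = 1.26 is another route to 14.

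There may also be an innocent origin for the effect size of 1. It could be the rounded 1.02 of the smaller contrast, exercise versus combined, used conservatively and printed beside the other contrast's means.

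All of this stands as a limit on the conclusion, but none of it removes the contradiction. Each route to 14 needs something that the article does not state (a one-sided test or a split alpha). The one-sided route also needs an effect size that the adjacent means and SD contradict. The split-alpha route leaves the second comparison at about 61%, so it cannot support the sentence that the same size is adequate there.

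**Conclusion.** Wrong as written, but below the level of a must-fix. The effect size of 1 contradicts the means and SD in the same sentence, which give 1.26. At the stated alpha of 0.05, 14 per group for 80% power follows only if d = 1 is combined with an undeclared one-sided test.

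The size of the problem depends on which input is right. At 14 per group and two-sided 0.05, tDCS versus combined has about 88% power on the printed means and SD, or about 70% if d = 1 is meant. For exercise versus combined, two-sided power is about 72%, so the adequacy claim holds at 80% only one-sided (82%). That last result assumes that SD 1.27 applies to this pair. All of these figures assume a normal parent distribution.

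**What to change.** Revise the Sample Size paragraph so that its figures agree:

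- Make the effect size match the means and SD: write d = 1.26 with SD 1.27. If d = 1 was intended for tDCS versus combined, give the SD that yields it together with its source. An SD of 1.6 should not be written in merely because it makes the division work.
- State whether the test is one- or two-sided, and the alpha used for each of the two comparisons with the combined arm.
- Restate the power at 14 per group for both comparisons. At two-sided 0.05 with SD 1.27 these are about 88% (tDCS versus combined) and about 72% (exercise versus combined, if that SD applies). Reword the sentence on adequacy for the second comparison to match.

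The cost is a text correction with no change in enrolment. The restated power for exercise versus combined may be less favourable than the article now implies.

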**Conclusions:**

We expect that the combination of tDCS and telemedicine programs will reduce pain perceived by patients with breast cancer and improve their mental well-being more effectively than single interventions. Furthermore, we assume that this home-based approach will also improve patients’ participation in routine clinical care, reducing disparities in accessing health care processes. This integrated home care strategy could be useful for patients with breast cancer who cannot find relief from chronic pain with pharmacological treatments or for those who have limited access to care due to poor mobility or geographical barriers, thus increasing the patients’ empowerment and reducing health care costs.

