### Statistical Analysis

To evaluate the efficacy of the treatments, a statistical analysis will be conducted on the clinical scales, functional tests, and questionnaires using a dedicated software. Data distribution will be evaluated using Shapiro-Wilk tests. In the case of a normal distribution, statistical significance will be evaluated by applying parametric *t* tests and ANOVA for repeated measures. In case the assumption of a normal distribution is not supported, a nonparametric Wilcoxon-Mann-Whitney test will be used. Statistical analysis will be performed on all participants who complete the treatment required by the protocol. Participants who do not complete all phases of the study (ie, dropouts) will be excluded from the data analysis. Furthermore, as suggested by recent scientific literature, Bayesian statistics will also be applied using JASP open-source software in order to better estimate the possible absence of an effect of therapeutic strategy [58]. In particular, intragroup comparison analysis will be assessed using repeated measures ANOVAs (within subjects, time factors). Comparison of the subgroups (n=14 per group) will be performed using parametric or nonparametric hypothesis tests depending on the normality of the data distribution and corrections of type 1 errors. Finally, correlations will be performed between the VAS, patient demographics, and clinical data. All secondary outcomes will be evaluated by descriptive statistical analysis. Analysis will be carried out using SPSS Statistics (version 27; IBM).

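### The statement that 14 per group is also adequate for exercise versus combined therapy holds only for an uncorrected one-sided 0.05 test, which the protocol does not state and which conflicts with its promised type 1 error corrections

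*Protocol article*

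**What the plan says.** All references are to the protocol article.

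- **Sample Size.** The calculation is for the change in VAS, tDCS against combined therapy. The method is given as "A Wilcoxon-Mann-Whitney test was performed using G*Power V3 software". The planning effect size is 1. For the means, the section takes "a VAS change of 1.3 in the tDCS treatment group and 2.9 in the combined therapy group". For the spread it takes "an SD of 1.27 in both groups". The error rates are stated as "a type 1 error of 0.05; and a power of 80" per cent. It does not say whether the test is one-sided or two-sided. The result is 14 per group, 42 in all, with dropouts replaced.
- **Sample Size, closing sentence.** "A sample of the same size is adequate to demonstrate the difference in VAS between the exercise therapy group and the combined therapy group", with a reference to the same fibromyalgia study. No effect size, SD or power is given for this second pair.
- **Table 4.** The VAS changes are 1.296 (tDCS), 2.8981 (combined) and 1.598 (exercise).
- **Statistical Analysis.** The groups of 14 will be compared by parametric or nonparametric tests, "depending on the normality of the data distribution and corrections of type 1 errors". Neither the method nor the number of comparisons is named.
- **Abstract, Conclusions.** The authors expect the combination to reduce pain and "improve their mental well-being more effectively than single interventions".

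**The concern.** The adequacy sentence is a positive claim about power, made without a calculation. The expected difference for exercise versus combined (1.30) is smaller than for tDCS versus combined (1.60), so this is the harder of the two comparisons and limits what the trial can say about the combination. The sample size spends the whole 0.05 on one comparison, while the analysis promises to correct across comparisons.

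If 80% is taken at face value and the real figure is lower, a non-significant exercise comparison is more likely than planned. It could then be read as showing that adding tDCS to exercise brings nothing.

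**Working it through.** **Inputs.** Means come from Table 4. The SD of 1.27 comes from Sample Size, where it is stated for the tDCS and combined groups; using it for exercise is an assumption. There are 14 per group with equal allocation.

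**Method.** Wilcoxon-Mann-Whitney power by asymptotic relative efficiency with normal data: effective size n_e = n × 3/π, degrees of freedom 2n_e − 2, noncentrality d × √(n_e/2), power from the noncentral t distribution. For n = 14: n_e = 13.37, df = 24.74, √(n_e/2) = 2.585. Critical values are 1.709 (one-sided 0.05) and 2.061 (two-sided 0.05).

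**Step 1: reproduce the plan's 14.** With d = 1, noncentrality is 2.585.

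- One-sided 0.05: power 80.8% at 14 per group, and 14 is the smallest n that reaches 80%. Exact-test simulation gives 80.0%.
- Two-sided 0.05: power 70% at 14 per group; 18 are needed.

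At the stated effect size and type 1 error, only the one-sided reading gives 14.

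The stated means and SD do not give the stated effect size: (2.9 − 1.3)/1.27 = 1.26. That value needs 9 per group one-sided or 12 two-sided at 0.05. It reaches 14 only at two-sided 0.025, which is not the stated 0.05.

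**Step 2: exercise versus combined.** Difference = 2.8981 − 1.598 = 1.3001. d = 1.3001/1.27 = 1.024. Noncentrality = 1.024 × 2.585 = 2.647.

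| Type 1 error per comparison | One-sided: power at 14 (n for 80%) | Two-sided: power at 14 (n for 80%) |
|---|---|---|
| 0.05, uncorrected | 82% (14) | 72% (17) |
| 0.025, Bonferroni for 2 | 72% (17) | 61% (21) |
| 0.0167, Bonferroni for 3 | 65% (19) | 54% (23) |

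Exact-test simulation (40,000 runs) agrees within about one percentage point: 81%, 72% and 64% one-sided; 72%, 60% and 54% two-sided.

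**Step 3: sensitivity to the assumed SD.** At 14 per group and two-sided 0.05, 80% is reached if the common SD is about 1.15 (d = 1.3001/1.15 = 1.13). If the effect size of 1 is kept for the 1.6 difference, the SD must be 1.6. Then d = 1.3001/1.6 = 0.81, and power is 65% one-sided or 52% two-sided. That reading contradicts the stated 1.27, so nothing here rests on it.

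**Step 4: both comparisons together.** Three normal arms were simulated with the Table 4 means, SD 1.27, 14 per arm, a shared combined arm and exact Wilcoxon-Mann-Whitney tests. The chance that both comparisons succeed is about 78% at one-sided 0.05, 67% at two-sided 0.05 and 54% at two-sided 0.025 each.

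**The case against.** A reader might infer that Table 4 by itself makes the adequacy sentence false. It does not. The effect size for exercise versus combined (1.024) is slightly above the planning value of 1, so a sample adequate for the one is adequate for the other on the same test. The stated inputs yield 14 only with a one-sided test, and on that basis this pair has 82% power. That part of the objection stands: the sentence is consistent with the calculation that produced 14.

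The objection does not rescue the plan. No one-sided test is stated anywhere, and the article's Conclusion asks which treatment is most effective, which is not a one-directional question. Bonferroni for two or three comparisons puts this pair below 80% under either sidedness.

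Three further points limit the finding:

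- **The SD.** No SD is given for exercise, and the cited study is not available here. A common SD of about 1.15 would restore 80% at two-sided 0.05, though not under a further correction.
- **The correction.** Bonferroni is a strict choice. Holm would give this pair a power between the Bonferroni and the uncorrected figures. The method may properly sit in a full analysis plan; the difficulty is that the sample size claim allows for none.
- **The joint claim.** A reader might infer that the trial must win both comparisons. The protocol sets no such rule. The abstract states an expectation, and the words quoted from it concern mental well-being, not the VAS. The joint power is therefore relevant only if that claim is intended, and its absence is not an error of arithmetic.

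The planned Bayesian analysis of a possible absence of effect partly guards against misreading a null result. It does not correct the stated power.

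**Conclusion.** The concern holds in this limited form: the adequacy sentence is right for an uncorrected one-sided 0.05 test (about 82%) and not for the other bases examined. Power is about 72% at two-sided 0.05. With Bonferroni for two or three comparisons it is 72% or 65% one-sided and 61% or 54% two-sided. The favourable basis is unstated, and it conflicts with the corrections promised in the Statistical Analysis section.

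These figures rest on Table 4's means, on normal data and on an SD of 1.27 in the exercise arm. The arithmetic is firm given those inputs. Which sidedness the sponsor intended cannot be settled from the document.

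**What to change.** 1. State whether the test is one-sided or two-sided, and name the correction and the comparisons it covers.
2. Replace the adequacy sentence with the power that those choices give. For an uncorrected two-sided test, for example: *For combined versus exercise (difference 1.30, SD assumed 1.27, d = 1.02), 14 per group gives about 72% power at two-sided 0.05.* If another basis was meant, take the figure from the table in the working.
3. Decide what is to be claimed. If combined therapy is to be declared better than both single treatments, say that both comparisons must reach p < 0.05. Because both must succeed, no alpha split is needed; give the joint power, about 67% two-sided. If either comparison may be claimed alone, use Holm.
4. While editing, reconcile the effect size of 1 with the stated means and SD, which give 1.26.

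The cost is a few sentences. No extra patients are required; the only downside is a less favourable stated power.

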### Statistical Analysis

To evaluate the efficacy of the treatments, a statistical analysis will be conducted on the clinical scales, functional tests, and questionnaires using a dedicated software. Data distribution will be evaluated using Shapiro-Wilk tests. In the case of a normal distribution, statistical significance will be evaluated by applying parametric *t* tests and ANOVA for repeated measures. In case the assumption of a normal distribution is not supported, a nonparametric Wilcoxon-Mann-Whitney test will be used. Statistical analysis will be performed on all participants who complete the treatment required by the protocol. Participants who do not complete all phases of the study (ie, dropouts) will be excluded from the data analysis. Furthermore, as suggested by recent scientific literature, Bayesian statistics will also be applied using JASP open-source software in order to better estimate the possible absence of an effect of therapeutic strategy [58]. In particular, intragroup comparison analysis will be assessed using repeated measures ANOVAs (within subjects, time factors). Comparison of the subgroups (n=14 per group) will be performed using parametric or nonparametric hypothesis tests depending on the normality of the data distribution and corrections of type 1 errors. Finally, correlations will be performed between the VAS, patient demographics, and clinical data. All secondary outcomes will be evaluated by descriptive statistical analysis. Analysis will be carried out using SPSS Statistics (version 27; IBM).

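### Name one baseline-adjusted between-arm analysis in place of the normality-gated tests, whose only nonparametric fallback is a two-sample test and which include no baseline covariate

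*Protocol article*

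**What the plan says.** The Statistical Analysis section of the protocol article sets these rules:

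- Normality is checked with Shapiro-Wilk. If it holds, t tests and repeated-measures ANOVA follow. If not: "In case the assumption of a normal distribution is not supported, a nonparametric Wilcoxon-Mann-Whitney test will be used". No other nonparametric method is named.
- Within arms: "intragroup comparison analysis will be assessed using repeated measures ANOVAs (within subjects, time factors"). No arm-by-time term appears.
- Between arms: the three groups of 14 are compared by parametric or nonparametric tests, according to normality, with a correction for type 1 error whose method is not given. No covariate is named.
- The opening sentence of the section applies the efficacy analysis to scales and questionnaires generally. Near its end stands: "All secondary outcomes will be evaluated by descriptive statistical analysis". The abstract's Conclusions nevertheless expect the combination to "improve their mental well-being more effectively than single interventions".

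The Sample Size section powers a between-arm difference in VAS change from the start of treatment to 1 week, using Wilcoxon-Mann-Whitney. The Intervention section sets five assessments, including baseline.

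**The concern.** The article fixes these rules, so they are not simply detail left to an analysis plan. Four things follow.

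1. The data choose the test, so neither the primary test nor the quantity it estimates is settled in advance.
2. The single named fallback can serve one pair of arms at one visit. It cannot stand in for a repeated-measures ANOVA over five visits, give a three-arm test or test arm-by-time. If normality fails, part of the plan has no stated method.
3. Within-arm time effects do not compare treatments. If one arm is significant and another is not, that does not show that the arms differ.
4. Baseline VAS is collected but is not used as a covariate. With 14 per arm, that gives up precision the trial needs, above all for combined versus exercise therapy, a contrast for which the Sample Size section calls the same sample adequate.

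In addition, the same section both tests questionnaires and calls secondary outcomes descriptive only. A reader cannot tell what evidence will support a comparative statement on mental well-being.

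**Working it through.** **Inputs (Sample Size section).** "a VAS change of 1.3 in the tDCS treatment group and 2.9 in the combined therapy group"; "an SD of 1.27 in both groups"; "a type 1 error of 0.05; and a power of 80" per cent; 14 per arm. Table 4 gives 1.598 for exercise therapy. The differences are 2.9 − 1.3 = 1.6 (combined versus tDCS) and 2.9 − 1.6 = 1.3 (combined versus exercise). The baseline-to-follow-up correlation r is not in the article; r = 0.3 to 0.7 is assumed.

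**The plan's own figure.** The calculation was run "with an effect size of 1 and assuming the following parameters". At d = 1, one-sided 0.05, normal parent, Wilcoxon-Mann-Whitney needs 14 per arm (power 0.808), which matches. Two-sided at d = 1 it needs 18 per arm, and power at 14 is 0.70. The listed means and SD imply d = 1.6/1.27 = 1.26, not 1. That mismatch is a separate point. The figures below use the listed differences and SD, two-sided.

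**Formulas.** Power comes from the noncentral t distribution with noncentrality (Δ/SD)·√(n/2).

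- t test on change: SD = 1.27, df = 2·14 − 2 = 26.
- Wilcoxon-Mann-Whitney: n is replaced by n·3/π = 13.37.
- Baseline-adjusted: with equal SD σ at both times, the SD of change is σ√(2(1 − r)) and the residual SD is σ√(1 − r²). Their ratio is √((1 + r)/2), so SD = 1.27·√((1 + r)/2) and df = 2·14 − 3 = 25.

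**Worked case.** Δ = 1.3. Unadjusted: 1.3/1.27 = 1.024; 1.024·√7 = 2.71; power 0.74. Adjusted at r = 0.5: SD = 1.27·√0.75 = 1.10; 1.3/1.10 = 1.182; 1.182·√7 = 3.13; power 0.85.

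| Analysis, 14 per arm | Δ = 1.3, α 0.05 | Δ = 1.3, α 0.025 | Δ = 1.6, α 0.05 |
|---|---|---|---|
| t test on change | 74% | 63% | 89% |
| Wilcoxon-Mann-Whitney on change | 72% | 61% | 88% |
| Adjusted, r = 0.3 (SD 1.024) | 90% | 83% | 98% |
| Adjusted, r = 0.5 (SD 1.100) | 85% | 77% | 96% |
| Adjusted, r = 0.7 (SD 1.171) | 81% | 71% | 93% |

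The 0.025 column is Bonferroni for two contrasts. For 80% power at Δ = 1.3 and α 0.05, the adjusted analysis needs 11, 13 or 14 per arm, against 17 for either unadjusted test. The formula ignores chance baseline imbalance. A simulation with normal data at r = 0.5 (6,000 runs) gave 83% adjusted and 73% for the t test, so the formula is slightly optimistic for the adjusted analysis, but the gap remains.

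**The gate.** In the same simulation of the two-arm comparison, Shapiro-Wilk rejected normality in 9-10% of comparisons with truly normal data, and in only 42-44% when follow-up error was exponential. Type 1 error of the gated choice was 0.046 and 0.050.

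**Within-arm tests.** Suppose all three arms truly improve by 1.0 point (SD 1.27). A before/after test at n = 14 is significant in 77.9% of arms (simulation, 20,000 runs). Some arms but not all are significant with probability 1 − 0.779³ − 0.221³ = 0.52. At a common improvement of 0.7 points it is 75%, and at 1.3 points 17%. The arms are identical in each case.

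**The case against.** The strongest reply is that the plan contains a valid core. It compares the arms and corrects for type 1 error, the Sample Size section powers a between-arm difference, and unadjusted change is unbiased under randomisation. On that view baseline adjustment is an efficiency choice, and the missing counterpart for repeated data is detail for a fuller document. Much of this stands. Baseline adjustment is indeed a gain in efficiency, and the contrast actually powered (1.6) already has 88-89%. If the intended test is one-sided, which the article does not say, the 1.3 contrast has 82-84% unadjusted.

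Several stronger readings are tempting, and the article does not support them:

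- *Efficacy will be judged within arms only.* No sentence says so, and a between-arm comparison is planned.
- *Baseline VAS is ignored.* It enters through change from baseline and as a time level in the ANOVA. What is absent is a baseline-adjusted between-arm comparison.
- *Wilcoxon-Mann-Whitney will be run on paired visits.* The article does not state this. The Sample Size section uses the test properly, between two arms on change.
- *The gate inflates type 1 error.* The simulation shows none in the two-arm comparison.
- *Selection on VAS above 4 guarantees a sizeable improvement by regression to the mean.* Its size depends on a source population the article does not describe. It would be small if that population lay near the Table 4 baselines of 6.8 to 7.3.
- *The abstract's expectation on mental well-being is a planned inferential claim.* It is worded as an expectation.

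**Conclusion.** The point holds as a weakness of specification and efficiency, not as an invalid primary comparison. The test is not fixed in advance, the only named fallback does not cover three arms and five visits, and no baseline covariate or arm-by-time term is stated.

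The gain from adjustment is largest for combined versus exercise therapy. Power rises from 72-74% to 81-90%, or from 61-63% to 71-83% with Bonferroni for two contrasts, with the same 42 patients. After Bonferroni, 80% is reached only towards the lower end of the assumed correlations. For combined versus tDCS it rises from 88-89% to 93-98%.

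These figures assume the article's SD of 1.27 in every arm, equal SDs at baseline and follow-up, r between 0.3 and 0.7, two-sided testing and one visit. A mixed model over all visits was not evaluated.

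The contradiction between tested questionnaires and descriptive-only secondary outcomes is real and should be reconciled.

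**What to change.** Rewrite the Statistical Analysis section as follows:

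1. Remove the Shapiro-Wilk gate.
2. Name one primary between-arm analysis: a linear model for VAS with arm and baseline VAS. Alternatively, use a mixed model over the post-baseline visits with arm, visit, arm-by-visit and baseline VAS, and small-sample degrees of freedom such as Kenward-Roger.
3. Report combined minus tDCS and combined minus exercise therapy with 95% CIs at the 1-week visit used for the sample size, or at another visit named in advance.
4. State the multiplicity rule for these two contrasts, such as Holm, and whether tests are two-sided.
5. Keep a rank-based between-arm test of change as a sensitivity analysis.
6. Present within-arm changes descriptively, without p values.
7. Resolve the conflict on secondary outcomes by reporting between-arm estimates with CIs for the questionnaires, labelled secondary.

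The cost is wording: no new data, visits or patients. The model does not resolve the exclusion of participants who do not complete the study. That needs its own change to the analysis set.
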